### Participants

A purposive sampling approach will be taken with the following inclusion criteria for participants: Children (1) aged three to five years, (2) enrolled in a local kindergarten within the same territory as the research center (i.e., New Territories and Hong Kong), and (3) have no diagnosed neurodevelopmental, medical, or orthopedic condition that is contraindicated to moderate intensity physical activity or that requires special educational needs support. In previous research, a six-week gross motor skills training program led to improved motor proficiency, with effect sizes ranging from 0.28 to 0.45 (Brian and Taunton, 2018). Taking a conservative approach, it was calculated that to achieve 80% power (two-tailed alpha at 0.05), with an effect size of 0.28, and accounting for between-group and within-group interactions, a total sample of 144 is required to compare two groups (i.e., training and control) at four testing points. Accounting for 10% potential attrition rate, 79 participants per group (*N* = 158) will be recruited. The participants will be randomly allocated as a group (i.e., one intact kindergarten class) to either training or active control. Typical kindergarten classes in Hong Kong have about 20 to 30 pupils; hence, three to four classes will be allocated to each group (i.e., training and active control). To control for a cluster effect and socioeconomic status being a potential confounder, we had recruited a local kindergarten with at least eight kindergarten classes from a middle-class area.

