#### Outcome: Gross Motor Skills

The standardized Test of Gross Motor Development – 3rd Edition (TGMD-3; Ulrich, 2017, 2019) – will be used to measure gross motor skills proficiency. TGMD measures gross motor skills development of children (Ulrich, 2000) and had been widely used in research and practice (e.g., Chow and Chan, 2011; Bandeira et al., 2020). TGMD-3 is the recently updated version and had been found to have high levels of validity, internal consistency, and reliability (Webster and Ulrich, 2017).

Test of Gross Motor Development-3 (Ulrich, 2019) consists of two sub-scales: locomotor (run, gallop, skip, jump, hop, and slide) and object control skills (two-hand strike, one-hand strike, dribble, catch, kick, overhand throw, and underhand throw). For each skill, the examiner will demonstrate the skill, after which the child will perform one practice trial and two scored trials. A skill is scored based on the presence (score of 1) or absence (score of 0) of each criterion in every trial; the score for each skill is the sum of all criteria scores from two trials. Depending on the skill, performance criteria range from three to five across skills. The highest possible raw scores for the locomotor and object control sub-scales are 46 and 54, respectively (highest possible overall score is 100). Post-hoc scoring will be performed by a rater with >5 years’ experience using TGMD for research and clinical purposes. Raw sub-scale scores and total scores will be analyzed as has been done in other studies (Allen et al., 2017; Webster et al., 2019), particularly because the current normative data is based on North American populations.

It is noted that TGMD-3 tests thirteen gross motor skills (i.e., six locomotor and seven object control skills), while the training program targets three skills each among the locomotor, object control, and stability components of fundamental movement skills; these were found to be consistent with the local curriculum context. Because developmental progressions are typically found between skills and between components of fundamental movement skills (Donnelly et al., 2017), we expect that TGMD-3 will be able to capture consequent changes following the training program.

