### Data Analysis

A two-group growth model for intervention studies (Muthen and Curran, 1997) will be fitted to the outcomes data. Growth curves will be fitted to the repeated measures with separate random intercepts and slopes estimated for the training and active control groups. The random intercepts capture individual differences in skills at commencement. The intercepts will be regressed on participant characteristics (i.e., sex, age, body composition, fine motor skills, and physical activity), with the latter acting as explanatory variables for the observed individual differences. A separate but parallel model will be estimated with the intercepts set at the final follow-up to examine the extent to which the same characteristics explain differences at that final data point.

Training effects will be evaluated using random slopes fitted to the data from the training and active control groups. For both groups, separate slopes will be fitted to describe (a) the normative growth observed and (b) growth that deviates from the normative pattern that can be attributed to training. Whether the mean of this second curve deviates significantly from zero serves as a test for the effects of training. Shared variance attributable to children belonging to the same class will be corrected for potential clustering effects by using the complex sampling procedure in Mplus 8.0 (Muthén and Muthén, 2017).

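### Age is adjusted for in the growth intercepts but not in the slopes that carry the training effect; with 6 to 8 randomised classes, a chance age gap between arms could enter that effect

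*Protocol article*

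**What the plan says.** **Allocation (Protocol article, Participants).** The unit is the class: "The participants will be randomly allocated as a group (i.e., one intact kindergarten class) to either training or active control". There are few units: "three to four classes will be allocated to each group (i.e., training and active control", so 6 to 8 in total. They come from one site: "we had recruited a local kindergarten with at least eight kindergarten classes from a middle-class area". The reasons given for using one site are the cluster effect and socioeconomic status; age is not mentioned. The eligible age range is wide for motor and cognitive outcomes: "Children (1) aged three to five years".

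**Outcome scale (Outcome: Gross Motor Skills).** The TGMD-3 is not age-normed in the analysis: "Raw sub-scale scores and total scores will be analyzed as has been done in other studies".

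**Model (Data Analysis).** Age enters in one place: "The intercepts will be regressed on participant characteristics (i.e., sex, age, body composition, fine motor skills, and physical activity". A second model re-centres time: "A separate but parallel model will be estimated with the intercepts set at the final follow-up", with the same characteristics as predictors of that intercept. The training effect sits in another parameter, the mean of the growth curve that departs from the normative one: "Whether the mean of this second curve deviates significantly from zero serves as a test for the effects of training". No covariate is named for either slope. Clustering by class is handled with the complex sampling procedure in Mplus.

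**The concern.** The age adjustment and the test of training act on different parts of the model. Regressing intercepts on age removes an age-related difference in starting level. Moving the intercept to final follow-up shows how far age explains level at that time, but still leaves the slopes unadjusted. If older and younger children improve at different rates, and the arms differ in mean age, the arms will have different average slopes without any effect of training. The model has nowhere to put that difference except the deviation slope. The complex sampling correction changes the standard error, not the estimate, so it does not remove it.

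A difference in mean age between arms is a practical possibility because so few classes are randomised. What is at stake is the interpretation of the single realised comparison, especially for raw scores over an age range in which skills change quickly.

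**Working it through.** **1. The plan's own figures.** The article gives no figure for age balance or for growth by age, so there is none to reproduce on this point. Its planning effect is 0.28, metric not named. The stated total of 144 is reproduced if 0.28 is read as Cohen's f with 3 numerator df: lambda = 0.28² x 144 = 11.29, denominator df 140, power 0.803. On that reading 0.28 is not a difference in SD per year, so the slopes below should not be expressed as a share of it.

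**2. Chance gap in mean age.** Inputs from Participants: 6 or 8 classes, ages three to five. Assumptions: classes are formed by year level, with mean ages 3.5, 4.5 and 5.5, and are split equally and without restriction. Every allocation was enumerated (20 for 3 v 3, 70 for 4 v 4).

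| Classes per year level | SD of gap (y) | Gap in years (number of allocations) | Gap ≥ 0.5 y | Gap ≥ 1 y |
|---|---|---|---|---|
| 2/2/2 | 0.73 | 0 (8), 0.67 (8), 1.33 (4) | 60% | 20% |
| 3/3/2 or 2/3/3 | 0.59 | 0.25 (42), 0.75 (22), 1.25 (6) | 40% | 8.6% |
| 3/2/3 | 0.65 | 0 (18), 0.5 (36), 1.0 (12), 1.5 (4) | 74% | 23% |
| 3/3, two levels only | 0.45 | 0.33 (18), 1.0 (2) | 10% | 10% |
| 4/4, two levels only | 0.38 | 0 (36), 0.5 (32), 1.0 (2) | 49% | 2.9% |

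Check on the first row: the variance of the gap is 4S²/n, where S² is the variance of class mean age with divisor n − 1. Here S² = 4/5 = 0.8, so the variance is 4 x 0.8/6 = 0.533 and the SD is 0.73.

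**3. From age gap to training effect.** Let growth rate change by g SD/year for each year of age, and let the arms differ by D years in mean age. With age on the intercept only, the spurious slope difference is about g x D. The documents give no g; 0, 0.1 and 0.2 are shown as a range.

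| D (y) | g = 0 | g = 0.1 | g = 0.2 |
|---|---|---|---|
| 0.67 | 0 | 0.07 | 0.13 |
| 1.0 | 0 | 0.10 | 0.20 |
| 1.33 | 0 | 0.13 | 0.27 |

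**4. Simulation check.** Four waves of data were generated with no training effect: three classes of 24 per arm, 400 replicates, assumed times 0, 0.33, 0.75 and 1.08 years, and the training arm younger. A linear growth model with an arm difference in slope was fitted. This is simpler than the two-curve model in the plan, but the age adjustment sits in the same place.

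| g | D (y) | Age on intercept only | Age also on slope |
|---|---|---|---|
| 0 | 0.67 | −0.006 | −0.007 |
| 0 | 1.33 | 0.001 | 0.004 |
| 0.1 | 0.67 | 0.066 | −0.001 |
| 0.1 | 1.33 | 0.136 | −0.008 |
| 0.2 | 0.67 | 0.146 | 0.016 |
| 0.2 | 1.33 | 0.275 | 0.005 |

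The intercept-only results follow g x D. With age on the slope as well, every result is within 0.02 of zero.

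**The case against.** A reader might infer that the trial randomises with no balancing by year level. The documents do not say that. They are silent on the allocation procedure, and a condensed article commonly leaves stratification to the full protocol. That objection stands, so the point rests on where age is placed in the model, which the article does state.

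The article never says that classes are formed by age, nor which classes will enter. The mixes above are illustrations, and if classes mix ages evenly the gaps would be much smaller. This stands as a condition.

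A reader might also infer that the training effect is biased on every raw-score outcome. That is too strong. Under randomisation the imbalance averages out over allocations, and age differences in starting level are absorbed by the adjusted intercepts. Only age-dependent growth leaks through, and the documents offer no evidence of it. It is plausible for bounded scores such as the HTKS (0 to 40) at these ages, but plausibility is all that can be claimed. Raw scoring in place of norms is stated only for the TGMD-3. Nor do the documents show that age dominates the variance between classes or limits power; they give no outcome variance by class.

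Finally, the article does not expressly rule out slope covariates, and its introduction promises that influencing factors will be accounted for. But it lists what the intercepts are regressed on, twice, and gives nothing for the slopes. The follow-up-centred model does not fill that gap.

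**Conclusion.** The point holds as a conditional, low-cost improvement. The stated model adjusts starting level and follow-up level for age, but not the slope on which training is judged. With three year levels of classes (assumption), a gap of at least 1 year in mean age arises by chance in about 9 to 23% of allocations of eight classes and 20% with six; gaps of 0.5 year or more arise in 40 to 74%. With only two year levels the chance of a 1-year gap is 3 to 10%. If growth rate also varies by 0.1 to 0.2 SD/year per year of age (assumption), a gap of 0.67 year puts about 0.07 to 0.13 SD/year into the estimated training effect, in either direction. If either assumption fails, the distortion is small or nil. It does not show that the design is invalid or that the estimator is biased in expectation.

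**What to change.** **Analysis, in any case.** Regress the growth slopes, as well as the intercepts, on child-level baseline age. The normative slope should carry the same age coefficient in both arms, so that each arm's expected growth matches its own ages. The deviation slope should also be regressed on age, with age centred at the overall sample mean, so that the tested parameter is the training effect at that age. Age is already a named covariate, so no new data are needed. The cost is one coefficient per slope and some precision if the arms differ much in age. Child-level age spends fewer class-level degrees of freedom than year-level indicators.

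**Allocation, only if not yet done.** Randomise classes within year level where the numbers per level are even; with 2/2/2 this gives a gap of zero in all 8 permitted allocations. Otherwise draw at random from the allocations with a small arm difference in mean class age: 42 of 70 with a gap of 0.25 year for 3/3/2, or 18 of 70 with no gap for 3/2/3. A rule that arms may differ by at most one class per level is not a good substitute. With 3/2/3 it forces 2/1/1 against 1/1/2, that is mean ages 4.25 and 4.75, so all 36 permitted allocations have a 0.5-year gap and all 18 with no gap are excluded. The cost is a smaller set of permitted allocations.

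If allocation is already done, only the slope adjustment applies. The report should then state how classes were formed and allocated, and give mean age by arm.

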### Procedures

Random allocation will be at group level because the intervention is to be delivered in the context of kindergarten classes. Figure 1 illustrates the planned progress of participants through the study, following the flow diagram recommended by the Consolidated Standards of Reporting Trials (CONSORT; Schulz et al., 2010). Following receipt of parental informed consent, participants’ parents will be invited to complete a questionnaire ascertaining background information about the child, including typical daily activities and other learning (e.g., phonics and music) and physical (e.g., after-school sports and cycling) activities outside of the kindergarten. It is expected that parents will take about 20 to 30 min to complete the questionnaire. Measurement of covariate and outcome variables will be conducted across four time points, with the training program commencing after the first measurement (see Table 1 for schedule of implementation).

**Figure 1 fig1:**
[figure not shown]
Participants’ planned progress through the study.

**Table 1 tab1:** Schedule of measurements and training.

Measurement/Training	M1	T1	M2	T2	M3	M4
Physical growth: height (cm) and body mass (kg)	•					
Gross motor skills proficiency	•		•		•	•
Fine motor skills	•					•
Physical activity and sedentary behavior	•					•
Executive function	•		•		•	•
Social competence	•		•		•	•
Intervention/active control		•		•		

*M1, baseline measurement; T1, term 1 training; M2, mid-training measurement; T2, term 2 training; M3, post-training measurement; and M4, follow-up measurement. Outcomes are measured across all time points; covariates are measured only at baseline and follow-up*.

Preliminary work was conducted with local kindergarten teachers, which identified a number of key design considerations for the movement training program. First, training will target fundamental movement skills comprising: object control (i.e., throwing, catching, and kicking), locomotion (i.e., running, jumping, and hopping), and stability (i.e., turning, rolling, and balancing; Ulrich, 2000; Donnelly et al., 2017). These specific skills were identified to be consistent with the expectations of the curriculum guide for kindergartens in Hong Kong (Curriculum Development Council, 2017). Second, 20-min training sessions, three times per week, were deemed feasible in the context of the typical programming of local kindergartens. Third, the program duration was balanced to be both evidence-informed and fit for the local context. Significant movement skills improvement was evident following eight weeks of error-reduced training (Capio et al., 2018) or six weeks of training delivered by early childhood teachers (Brian et al., 2017). However, it was noted that eight weeks of fundamental movement skills training did not improve cognitive functioning of early primary school children (Lee et al., 2020). Therefore, the program duration in this study will be extended to enable motor development (as opposed to skill acquisition). Working around the school terms and breaks of the local curriculum, a 10-week intervention was deemed feasible in each of the two semesters of one school year. Finally, it was determined that teachers will be trained to deliver the intervention, supported by project assistants who had been trained in error-reduced approach to fundamental movement skills training. This was deemed an important consideration because teacher-led interventions in early childhood settings have been shown to benefit children (Jones et al., 2016). Teachers’ training will consist of the knowledge base for the error-reduced learning approach, the rationale for each lesson plan, and the performance measures that would serve as the basis for progression.

Errors will be minimized by specifically manipulating equipment size and training conditions, such that the initial sessions are suitably easy to allow successful movement performance. Progressive increments in task difficulty will follow when each child in a class is able to display successful performance ≥75% of the time at a task (e.g., task completion: 6 out of 8 attempts are successful). Equipment manipulation has been shown to be feasible in field-based studies (e.g., Buszard et al., 2014), and delivering error-reduced motor skills training in class settings is feasible (Capio et al., 2015). Class-based training activities were therefore designed in partnership with local kindergarten teachers, where equipment and environment set-up, procedures, and progressions were identified (see Table 2 for a sample).

**Table 2 tab2:** Sample activity for the movement training program.

Skill	Equipment/Set-up	How	Progressions	Performance measure
Hopping	*Equipment* Circle mats Masking tape or carpet squares *Setting* Indoor or outdoor Set-up rows of three single mats and three double mats	The teacher will demonstrate hopping on one leg through the row of single mats, and jumping (two legs) through the row of double mats The children will take turns in hopping on single mats and jumping on double mats. Hopping will be practiced with both right and left legs Note that the focus is on hopping, but jumping is included for activity variation	Initial session will be hopping on the spot, while the children hold on to support (hold on to shoulders of classmates) Hopping in place without holding on to support Hop through the row of single mats in pairs (children holding hands for support). Hop through the row of single mats individually *Equipment manipulations to further increase task difficulty* Increase the number of mats in a row Increase the distance between consecutive mats	Successful hopping on the spot/in place at least 6 out of 8 trials in each bout to progress Successful hopping through a full row of mats at least 3 out of 4 rounds to progress

*Group progression will take place when each child in a class is able to achieve ≥75% successful performance*.

The active control group will participate in the typical physical activities currently being implemented in their kindergartens in the context of the local curriculum guide. Details of the activities (including the parameters, such as repetitions and bouts) completed during the study period will be documented for both the active control and the training group to ensure that activities are delivered as planned (i.e., fidelity check). The instruction approach for the active control groups will also be identified and documented (e.g., direct instruction).

### Measures

To measure immediate and sustained effects of training on the outcomes, assessments will be performed prior to training (baseline, M1), at the end of the first term (mid-training, M2), at the end of the second term (post-training, M3), and four months after the end of training (follow-up, M4). Participants’ performances in the tests for fundamental movement skills, executive function, and working memory will be recorded on videos and scored post-hoc by designated research staff who were not involved in the test administration (i.e., blinded to participants’ allocation to training or active control groups). A random sample of video recordings (i.e., 10%) will be scored by a second set of designated research staff to establish inter-rater reliability.

#### Outcome: Gross Motor Skills

The standardized Test of Gross Motor Development – 3rd Edition (TGMD-3; Ulrich, 2017, 2019) – will be used to measure gross motor skills proficiency. TGMD measures gross motor skills development of children (Ulrich, 2000) and had been widely used in research and practice (e.g., Chow and Chan, 2011; Bandeira et al., 2020). TGMD-3 is the recently updated version and had been found to have high levels of validity, internal consistency, and reliability (Webster and Ulrich, 2017).

Test of Gross Motor Development-3 (Ulrich, 2019) consists of two sub-scales: locomotor (run, gallop, skip, jump, hop, and slide) and object control skills (two-hand strike, one-hand strike, dribble, catch, kick, overhand throw, and underhand throw). For each skill, the examiner will demonstrate the skill, after which the child will perform one practice trial and two scored trials. A skill is scored based on the presence (score of 1) or absence (score of 0) of each criterion in every trial; the score for each skill is the sum of all criteria scores from two trials. Depending on the skill, performance criteria range from three to five across skills. The highest possible raw scores for the locomotor and object control sub-scales are 46 and 54, respectively (highest possible overall score is 100). Post-hoc scoring will be performed by a rater with >5 years’ experience using TGMD for research and clinical purposes. Raw sub-scale scores and total scores will be analyzed as has been done in other studies (Allen et al., 2017; Webster et al., 2019), particularly because the current normative data is based on North American populations.

It is noted that TGMD-3 tests thirteen gross motor skills (i.e., six locomotor and seven object control skills), while the training program targets three skills each among the locomotor, object control, and stability components of fundamental movement skills; these were found to be consistent with the local curriculum context. Because developmental progressions are typically found between skills and between components of fundamental movement skills (Donnelly et al., 2017), we expect that TGMD-3 will be able to capture consequent changes following the training program.

